
**TABLE OF CONTENT**

FLOW CHART 9

INTRODUCTION 11

ETHICAL ASPECTS 13

STUDY OBJECTIVES 14

METHODS 15

STUDY TREATMENT 17

STUDY POPULATION 18

DATA MANAGEMENT AND STATISTICAL METHODS 20

PLAN FOR DISSEMINATION OF STUDY RESULTS 21

REFERENCES 22

| FORZA – Study flow chart | | | | |
| --- | --- | --- | --- | --- |
|  | **Pre-treatment**  **-6 months** | **Pre-treatment**  **0 month** | **Follow up**  **+1 month** | **Follow up**  **+6 months** |
|  | **(-6M)** | **(0M)** | **(1M)** | **(6M)** |
| *Demography* | [figure not shown] |  |  |  |
| *MS diagnosis and history* | [figure not shown] |  |  |  |
| *Clinical evaluation*  *(any changes in therapy, any relapses)* |  | [figure not shown] | [figure not shown] | [figure not shown] |
| *NfL* | [figure not shown] | [figure not shown] | [figure not shown] | [figure not shown] |
| *MEPs* | [figure not shown] | [figure not shown] |  | [figure not shown] |
| *OCT* | [figure not shown] | [figure not shown] | [figure not shown] | [figure not shown] |
| *EDSS* | [figure not shown] | [figure not shown] | [figure not shown] | [figure not shown] |
| *T25FW* | [figure not shown] | [figure not shown] | [figure not shown] | [figure not shown] |
| *MSWS12* | [figure not shown] | [figure not shown] | [figure not shown] | [figure not shown] |
| *9HPT* | [figure not shown] | [figure not shown] | [figure not shown] | [figure not shown] |
| *MOCA* | [figure not shown] | [figure not shown] | [figure not shown] | [figure not shown] |
| *SDMT* | [figure not shown] | [figure not shown] | [figure not shown] | [figure not shown] |
| *HADS* | [figure not shown] | [figure not shown] | [figure not shown] | [figure not shown] |
| *OAB* | [figure not shown] | [figure not shown] | [figure not shown] | [figure not shown] |
| *Brain MRI* | [figure not shown] | [figure not shown] | [figure not shown] | [figure not shown] |
| *MRI with DWI and 1H-MRI*** | [figure not shown] | [figure not shown] | [figure not shown] | [figure not shown] |
| *Treatment assumption* |  | [figure not shown]* |  |  |
| *Treatment compliance* |  |  | [figure not shown] | [figure not shown] |
| *AE collection* |  |  | [figure not shown] | [figure not shown] |
| ** Only after the execution of all assessments*  ***Only for a subgroup of patients* | | | | |

|  |  |
| --- | --- |
|  |  |
|  |  |
|  |  |
|  |  |

## INTRODUCTION

Background

Multiple sclerosis (MS) is the first cause of progressive neurological disability in young adults.

In the relapsing-remitting (RR) form of the disease, the pathophysiology is dominated by the inflammatory response, and a range of effective immune-modulating therapies have been successfully developed. In progressive MS (PMS), different pathophysiologic mechanisms seem to interact, resulting in myelin damage and neurodegeneration through incompletely understood events. Therefore, while targeting inflammatory pathways has advanced the efficacy of treatments in RRMS, progressive forms lag behind.^1^ Furthermore, progression of disability develops in MS independently of disease phase: disability can accrue insidiously also during the RR phase of the disease^2,3^. Furthermore, a significant percentage of people with RRMS, even though treated with the most effective therapies, still develop secondary progressive MS (SPMS)^4^.

**Rationale for the study**

Osmotin is a protein initially characterized as associated with stress adaptation in plant cells^5^. Actinidia Deliciosa plants overexpressing the osmotin protein were developed at the University of Tuscia in Italy, and tested for ten years for their improved agronomic and nutritional qualities^6^. In addition, it has been shown in different plant species that the overexpression of the osmotin plant gene increases the production of flavon-3ols and other anti-inflammatory plant compounds^30^. In mammals, osmotin binds the adiponectin receptor due to the 3D structure homology between the two proteins^7^. As such, it may share some of the anti-inflammatory effects of adiponectin^8-10, 28^. Indeed, this appears to be the case with the attenuation of LPS-induced neuroinflammation^11^ and with preventive effects on vascular inflammation in atherosclerosis^10^. Osmotin also protects against glutamate-induced synaptic dysfunction and neurodegeneration in the rat brain, and attenuates LPS-induced neuroinflammation^11^. However, adiponectin also has pro-inflammatory functions^12^. High and low molecular weight isoforms of the adiponectin molecule may play different roles in inflammation^13,14^. This may explain conflicting results on the role of adiponectin in MS^15-25^. However, because osmotin and adiponectin have different amino acid sequences, with the exception of the active site^29^, osmotin may not manifest the negative effects that may be associated with adiponectin polymers. Additionally, the anti-inflammatory effects of Actinidia plants are well-documented^27^.

Based on these premises, a nutraceutical product (commercial name Forza) has been developed by 9th Dimension Biotech, Inc., consisting of the lyophilised leaves of the A. Deliciosa plants bioencapsulating recombinant osmotin, with the goal of offering the combined benefits of the osmotin protein in conjunction with the enhanced anti-inflammatory properties of the bioengineered A. Deliciosa plants to consumers. In fact, as recently as in 2016, it has been shown that the bioencapsulation of protein drugs in lyophilized plant cells represents an ideal method of oral protein drug delivery to patients, which surpasses all other methods of protein drug delivery both in safety and efficacy^26^. Therefore, it may be worth exploring the effects of Forza in MS, where Forza may play both anti-inflammatory and neuroprotective effects. Considering the strong need to identify therapies for the progressive forms of the disease, we here propose to explore the effects of Forza in PMS. Moreover, the low impact of current therapies in PMS may not overshadow possible effects of Forza, something that would probably happen with high efficacy treatments in RRMS.

## ETHICAL ASPECTS

After the approval of the Ethic Committees (EC), this study will be conducted in accordance with the study protocol, the current version of the Declaration of Helsinki, applicable Good Clinical Practices (GCP) guidelines and with the specific Italian regulations on non-interventional studies.

Before collecting data, the patients must sign and date the informed consent form having been previously reviewed and approved from the Ethical Committee.

By signing the protocol, the scientific coordinator will be responsible for maintaining the methodological accuracy of the study, both in the design phase and in the evaluation of results.

## STUDY OBJECTIVES

**Primary objective**

The study aims to address the following primary objective:

- Verify the safety of Forza in PMS during the entire treatment period.

**Secondary objectives**

Secondary objectives of the study are:

- Exploring the clinical and biological efficacy of Forza in PMS both after one month and six months of treatment or at the end of the study (in case of early withdrawal).

## METHODS

**Study design**

This is a prospective, multicenter, single-arm non-interventional study. It consists of a first visit six months before the assumption of osmotin (-6M), in which the investigators will inform patients about the study design and objective and the possibility to take part of it.

Then, only after having obtained a written informed consent, demographics characteristics and info about MS history will be collected, and clinical evaluations and assessments will be performed.

During a subsequent baseline visit, six months after the first one, (0M) the same clinical evaluations and assessments will be performed and after their execution the treatment will be administered and taken by the patients.

Two post treatment follow up visits are planned at 1 month (1M) and six months (6M) after the baseline, in which the same clinical evaluations and assessments will be recorded.

Patients meet all inclusion/exclusion criteria will be included in the study after having provided their written informed consent.

They will undergo two pre-treatment assessments: at -6 months (-6M) and at baseline visit (M0) and two post-treatment assessments at month 1 (M1), and at month 6 (M6).

The treatment will consist in the oral administration of Forza capsules at a minimum dosage of 5 grams per day.

At each timepoint the following assessments will be evaluated:

- Electrophysiological (motor evoked potentials – MEPs; somatosensory evoked potentials – SEPs; visual evoked potentials – VEPs)
- Optical coherence tomography (OCT)
- Neurofilaments (NfL)

In addition, clinician assessed outcomes (CAO), patient reported outcomes (PRO) and performance measure (PF) will be acquired for investigating the following domains:

- Motor domain (Expanded Disability Status Scale – EDSS; Timed 25 Foot Walk - T25FW; 12-item Multiple Sclerosis Walking Scale - MSWS12; Nine-Hole Peg Test - 9HPT)
- Cognitive domain (Montreal Cognitive Assessment - MOCA; Symbol Digit Modalities Test - SDMT)
- Emotional domain (Hospital Anxiety and Depression Scale - HADS), and for the bladder domain (Overactive Bladder - OAB).

Brain MRI will also be obtained at each timepoint as standard of care procedure.

In order to investigate the potential effect of Forza on brain metabolism (concentration of glutamate, N-acetylaspartate, creatine, choline) and microstructure, a subgroup of 25 patients (enrolled at the University of Genoa) will undergo MRI with a multi-shell diffusion-weighted (DWI) sequence and proton magnetic resonance spectroscopy (1H-MRI) in addition to routine sequences.

Any changes on disease modifying therapy (DMT), any occurrence of adverse events during treatment period and any interruption of treatment will be recorded on the medical chart.

[figure not shown]

[figure not shown]

## STUDY TREATMENT

**Forza formulation**

Forza is a nutraceutical supplement provided in capsules, and it consists of lyophilised and pulverised kiwi leaves from bioengineered kiwi (Actinidia Deliciosa) plants overexpressing the tobacco protein Osmotin^6^. Osmotin is a non-toxic plant protein present in all fruits and vegetables, which plays a key role in plants’ stress response and survival. In plants, the overexpression of Osmotin leads to a increased production of flavon-3-ols and other key antioxidant compounds^30^. This plant protein is also a homologue of the human adipokine Adiponectin.

**Forza administration and assumption**

The treatment will consist in the oral administration of a minimum dosage of 5 grams per day of Forza, provided in the form of capsules. Each capsule will contain approximately 0.7g of Forza. The capsules will be administered at the rate of 4 capsules in the morning and 3 additional capsules in the evening for the entire duration of the trial.

**Forza accountability**

Forza is nutraceutical supplement produced at a CGMP facility by 9th Dimension Biotech, Inc. in the United States of America. 9th Dimension Biotech will be accountable for the production and delivery of Forza to FISM for the duration of the trial.

## STUDY POPULATION

**Sites and patients**

The study is planned to be conducted at the MS Centres of the San Martino Hospital in Genoa and of the Sapienza University of Rome.

Patients with a progressive form of MS either untreated or under their current therapy will be enrolled by the MS Centres of the San Martino Hospital in Genoa and of the Sapienza University of Rome.

**Estimated sample size**

A sample of fifty (50) patients guarantee a 90% power to detect a reduction of 20% in the neurofilament change rate (assuming a SD=40%) during the treatment period (6M-1M) as compared to the pre-treatment period (0M – -6M).

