| **Methods** | Patients meeting all inclusion/exclusion criteria will be included in the study after having provided their written informed consent.  They will undergo two pre-treatment assessments: at -6 months (-6M) and at baseline visit (M0) and two post-treatment assessments at month 1 (M1), and at month 6 (M6).  The treatment will consist in the oral administration of a minimum dosage of 5 grams per day of Forza, provided in the form of capsules. Each capsule will contain approximately 0.7g of Forza. The capsules will be administered as follow: 4 capsules in the morning and 3 additional capsules in the evening from baseline () to month 6 (M6).  At each timepoint the following assessments will be evaluated: electrophysiological (motor evoked potentials – MEPs; somatosensory evoked potentials – SEPs; visual evoked potentials – VEPs), optical coherence tomography (OCT), and neurofilaments (NfL).  In addition, clinician assessed outcomes (CAO), patient reported outcomes (PRO) and performance measure (PF) will be acquired for the motor domain (Expanded Disability Status Scale – EDSS; Timed 25 Foot Walk - T25FW; 12-item Multiple Sclerosis Walking Scale - MSWS12; Nine-Hole Peg Test - 9HPT), for the cognitive domain (Montreal Cognitive Assessment - MOCA; Symbol Digit Modalities Test - SDMT), for the emotional domain (Hospital Anxiety and Depression Scale - HADS), and for the bladder domain (Overactive Bladder - OAB).  Brain MRI will also be obtained at each timepoint as standard of care procedure.  In order to investigate the potential effect of Forza on brain metabolism (concentration of glutamate, N-acetylaspartate, creatine, choline) and microstructure, a subgroup of 25 patients (enrolled at the University of Genoa) will undergo MRI with a multi-shell diffusion-weighted (DWI) sequence and proton magnetic resonance spectroscopy (1H-MRI) in addition to routine sequences. |
| **Endpoints** | The primary outcome of the study will be safety, and the co-primary efficacy outcome will be a reduction in the NfL change over 1 and 6 months as compared to the pre-treatment NfL change. |
| **Statistical analysis** | The NfL percentage changes will be compared pre and post treatment within patients by a non-parametric paired Wilcoxon test. |
| **Expected results** | We expect to verify the safety of an add-on therapy with *Forza* in PMS and to obtain clinical, paraclinical and laboratory information on the effects of *Forza* in this condition. |
|  |  |

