**Statistical analysis**

All collected data will be analyzed using descriptive statistics. Continuous variables will be described with number of patients with valid observations, mean, standard deviation, median, minimum and maximum value. If necessary, additional descriptive statistics may be calculated (in particular, for non-normally distributed data, the median with interquartile range). Categorical data will be described by frequencies and related percentages within variable. A p-value of 0.05 will be used as the cut off for statistical significance (no statistical test will be used for safety data).

Any comparisons between pre- and post- changes in continuous variables will be evaluated with paired sample t-test or Wilcoxon signed rank-test, as appropriate.

In particular, all safety and efficacy data will be analyzed using descriptive statistics. Safety data will be assessed by reporting and describing all the adverse events. Decisions following the safety pattern will be discussed by the study investigators, but no logic based on statistical test was set.

Depending on the results of interest, a stratified or an exploratory analysis may be conducted.

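### The 1-month NfL change is tested against a 6-month pre-treatment change, and the sample size rests on a third, 5-month window; if NfL is rising, the 1-month test favours an inert product

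*Supplement*

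**What the plan says.** The synopsis (Endpoints) defines the NfL outcome thus: "co-primary efficacy outcome will be a reduction in the NfL change over 1 and 6 months as compared to the pre-treatment NfL change". The synopsis (Statistical analysis) gives the test: "The NfL percentage changes will be compared pre and post treatment within patients by a non-parametric paired Wilcoxon test".

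Visits are at -6M, 0M, 1M and 6M, and treatment starts at 0M once that visit's assessments are done (Methods, Study design). The only pre-treatment change available is therefore -6M to 0M, which is 6 months.

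The section Estimated sample size plans for "a reduction of 20% in the neurofilament change rate (assuming a SD=40"%), and gives the window as "during the treatment period (6M-1M) as compared to the pre-treatment period (0M – -6M"). The sample-size text in the synopsis also speaks of a change rate but names no window. Neither place gives the rate a time unit.

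The section Statistical analysis adds only a general rule: "Any comparisons between pre- and post- changes in continuous variables will be evaluated with paired sample t-test or Wilcoxon signed rank-test, as appropriate". The significance cut-off is 0.05, with sidedness not stated. The design is single-arm.

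**The concern.** A percentage change accumulates over time. If NfL is drifting upwards, a change measured over 1 month will be smaller than one measured over 6 months whether or not the product works. A paired test of the two raw changes reads that difference as a reduction. There is no control arm to reveal the drift, so the within-patient comparison has to deal with it, and it can do so only if the windows match or the changes are expressed per unit time.

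The synopsis gives the 1-month comparison the same standing as the 6-month one, so a favourable 1-month result could be reported as success on a co-primary outcome. Separately, the window used for sizing (6M-1M) is neither of the two in the endpoint. It begins a month after treatment starts, so an effect complete by 1M would not appear in it.

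**Working it through.** **1. The plan's own figure.** Inputs: difference 20, SD 40, power 90%, n = 50 (Estimated sample size); alpha 0.05 (Statistical analysis), taken as two-sided. The SD is taken as that of the paired difference, which the text does not say.

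- Normal formula: n = [(1.960 + 1.282) × 40/20]² = 42.03, so 43 patients. Power at n = 50 is 94.2%.
- Paired t-test: n = 44, power at 50 is 93.4%.
- Wilcoxon, relative efficiency 0.955: power at 50 is 92.3%. At the minimum efficiency of 0.864 it is 89.4%.

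So 50 patients for 90% power is reproduced, or is slightly conservative. No interval length enters the formula, so it cannot show which window was meant.

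**2. Window lengths from the visit schedule.**

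| Contrast | Treated window | Pre-treatment window | Named in |
|---|---|---|---|
| 1M-0M | 1 month | 6 months | Synopsis, Endpoints |
| 6M-0M | 6 months | 6 months | Synopsis, Endpoints |
| 6M-1M | 5 months | 6 months | Estimated sample size |

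**3. Expected contrast with no treatment effect.** Assume a constant-percentage rise of g per 6 months. The documents give no value for g. The change over m months is (1 + g)^(m/6) - 1, and the pre-treatment change is g.

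| g | 1 month | 1-month shortfall | 5 months | 5-month shortfall | 6 months |
|---|---|---|---|---|---|
| 5% | 0.82% | 4.18 points | 4.15% | 0.85 points | 5%, shortfall 0 |
| 10% | 1.60% | 8.40 points | 8.27% | 1.73 points | 10%, shortfall 0 |
| 20% | 3.09% | 16.91 points | 16.41% | 3.59 points | 20%, shortfall 0 |

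In relative terms the built-in reduction is about 84-85% for 1 month and 17-18% for 5 months.

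**4. How often a trial would show a false reduction.** Simulation with n = 50, no effect, a steady log-scale trend, independent visit SD 0.16 on the log scale (assumed; it gives a paired-difference SD of about 40-49 points for the contrasts anchored at 0M), and a two-sided Wilcoxon test at 0.05. The nominal rate in the favourable direction is 2.5%. Ranges are across independent runs.

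| g | 1M-0M | 6M-1M | 6M-0M |
|---|---|---|---|
| 5% | 9-11% | about 4% | 2-3% |
| 10% | 27-29% | about 6% | 2-3% |
| 20% | 71-74% | about 10% | 2-3% |

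One run put the 6M-1M rates slightly lower, at 3-7% across this range of g. A simpler calculation (paired t-test, SD of the difference fixed at 40 points) gives 11%, 31% and 83% for 1M-0M; 3.5%, 4.9% and 9.1% for 6M-1M; and 2.5% for 6M-0M.

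**5. Other trends.** With g = 0 every window has an expected contrast of 0. With a 10% fall per 6 months the 1-month change is -1.74% against -10%, a contrast of +8.26 points against the product, and the false favourable rate drops to about 0.1%.

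**6. A limit on step 3.** If NfL rises in a straight line on the absolute scale, the 0M-to-6M percentage change is also slightly below the pre-treatment one (9.1% against 10%, or 16.7% against 20%). That comes from the higher starting value at 0M, not from the window length.

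**The case against.** **The word rate.** The sample-size text speaks of a change rate. Read as change per unit time, the length artefact disappears. This has force, but no unit is given and the word is not carried into the endpoint or the test, which the synopsis states on percentage changes.

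**The matched window.** A reader might infer that every NfL comparison in the plan is biased. That is not so: 0M to 6M is as long as the pre-treatment window, and the synopsis endpoint already includes it.

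**The 5-month window.** It appears only in the sample-size sentence and is not named as an analysis. The relative reduction of about 17% may look alarming beside the 20% target. But if 20 and 40 are percentage points, as in the calculation above, the artefact is 1.7 to 3.6 points for rises of 10-20%. The mismatch between sections stands, but the bias from this window is small. The synopsis endpoint also covers the first treated month.

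**Dependence on the trend.** The 71-74% figure needs a 20% rise per 6 months, which compounds to 44% a year (1.2 × 1.2 = 1.44). The documents support no particular value, so the result is conditional.

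**Scope and weight.** A reader might extend the point to all continuous outcomes, or call NfL the only efficacy evidence. The general testing rule names no windows, the flow chart shows no 1M entry for motor evoked potentials, and the plan collects many other efficacy measures, also without a control. The section Study objectives makes safety the sole primary objective and efficacy secondary. The synopsis nevertheless calls NfL co-primary, and the study is sized on it.

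**Conclusion.** The point holds for the 1-month comparison and for the disagreement between the synopsis and the sample-size section. As written, the plan tests a 1-month percentage change against a 6-month one without time scaling. With a steady rise and an inert product, that test gives a false favourable result in about 9-11%, 27-29% and 71-74% of trials for 6-month rises of 5%, 10% and 20%, against a nominal 2.5%. These rates rest on an assumed trend and an assumed visit SD of 0.16 on the log scale. No trend means no bias, and a falling trend reverses it.

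For 6M-1M the rate is about 4-10%; the main fault there is inconsistency and the omitted first month. For 6M-0M a steady percentage trend leaves the error rate at nominal. The documents therefore do not support the inference that the whole NfL analysis is invalid, nor that 50 patients is the wrong number for the stated inputs.

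**What to change.** - Name one NfL efficacy test with equal windows: the change from 0M to 6M against the change from -6M to 0M. Preferably use the log scale, [ln NfL(6M) - ln NfL(0M)] - [ln NfL(0M) - ln NfL(-6M)], or a change per unit time, using actual sampling dates. A per-month percentage rate would also remove the length artefact, provided it is defined.
- In Estimated sample size, replace 6M-1M with 6M-0M, and say that the 20% and 40% refer to this contrast. Align the synopsis endpoint and analysis with it.
- Report the 1M NfL value descriptively, or against the value projected from the patient's pre-treatment slope, not as a test against the raw 6-month change.
- Apply the equal-window principle to any other outcome whose pre/post changes are tested.

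Cost: wording in the endpoint, sample-size and analysis text. No new visits, samples or patients are needed, and 50 patients stands if the planning inputs refer to the equal-window contrast. The 1M comparison loses its stand-alone claim to significance.
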